### Data analysis plan

Descriptive statistics and frequency tabulations will be generated on the number of hazards per home at each time point and the total time and cost per home for modifications. Pass scores for the home (number of items passed/total items) will be calculated as well as the prevalence of each individual hazard (out of *N* = 300). The mean, median, and range of costs per household and per injury prevention measure will be calculated. Homes with outliers for the number, duration, and cost of modifications will be identified and the characteristics associated with those homes will be noted. A paired analysis will be used to test the change in mean number of hazards present between HV1 and HV3. Additional analyses will be performed for individual hazards and modifications.

Maintenance of modifications is of particular interest, along with variables that are associated with higher rates of maintenance, which will be examined by comparing HV2 and HV3 data; this will be an analysis of proportion of modifications still in place at HV3 by outcome variable and by modification options. Frequency distributions for the additional variables of interest (sociodemographic characteristics, characteristics of the homes, participant knowledge, participant capacity to complete home modifications, participant satisfaction with the program, and perceived barriers and facilitators collected during the initial home visit by the Assessor) will be prepared. These variables will be used to conduct regression analyses to explain the hazard and maintenance outcomes described above as a function of referral source, sociodemographic characteristics, housing, knowledge, installer (homeowner/tenant and GHHI), and satisfaction. To explore the capacity of caregivers to install injury prevention measures, paired data from HV1 and HV2 will be used to compute change in mean number of hazards.

For the qualitative analysis, open-ended questions on the participant Follow-Up Surveys and key informant interviews of GHHI staff will be used to develop a codebooks based on the content of the participant follow-up surveys and key informant interviews. Thematic analysis will be utilized to code data, a process common in qualitative research. Separate thematic analysis will be completed for each group. Through that process, perceived barriers and facilitators to implementation and sustainability will be explained, and participants’ suggestions for improvements will be identified and highlighted in the results. Resulting themes that are responsive to the objectives will be reported using illustrative quotes. The analysis will highlight implications for improved implementation of the CHASE tool and hazard remediation procedures from the perspectives of residents and the installers. Additionally, we expect at least some emergent themes to highlight potential processes underlying the trends captured in our quantitative data analysis. These results will be reported to contextualize our quantitative findings and reinforce or qualify results suggesting relationships between certain variables of interest and the successful implementation of home modifications.

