## Methods

### Study design and setting

The CHASE Implementation Study will use quantitative and qualitative methods and a non-experimental design to estimate the magnitude of home injury risks, identify strategies for addressing those risks and sustaining those interventions, and calculate the costs of housing-related modifications to prevent childhood home injuries. The Johns Hopkins Institutional Review Board has approved this study protocol. The study will enroll clients from families living in Baltimore City or Baltimore County receiving housing services from Green & Healthy Homes Initiative (GHHI)’s home visiting programs. GHHI is a Baltimore-based non-profit organization that coordinates funding from government and private institutions to deliver cost-effective services that assess and remediate a range of home health hazards. GHHI and JHU have partnered over the past several years to increase the inclusion of injury risk identification and modification in existing GHHI programs.

Participating families will first receive two home visits from a housing assessor using the CHASE tool to identify injury hazards in the home, outline a workplan for remediation, and assess the short-term maintenance of home modifications. On a third visit, study data collectors will conduct the home assessment. During each home visit, the participant will complete a questionnaire and receive feedback with results from the home inspection.

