Home Visit 2 (HV2) will occur approximately 30 days after HV1. A GHHI Assessor will return to reinspect the home, completing another CHASE Home Assessment Form to identify which hazardous item(s) the participants were able to modify on their own. They will complete a new Family Feedback Form to inform the family about the remaining risks in the home or to communicate that the home has passed all of the CHASE assessment items. A Research Assistant will administer the Health Belief Questionnaire and conduct a Follow-Up Survey.

For participants who were unable to address all hazards identified during HV1 (e.g., because the family could not or did not have sufficient means to address the hazards identified with home modifications alone or by calling a contractor), the Assessor will draft a Scope of Work for completion of the needed modifications and arrange a time to return to the home with the GHHI Housing Intervention Services Team, a professional home modification team who will complete the installation of any incomplete home modifications as described in the Scope of Work.^2^ When modifications are needed outside the capacity of the Housing Intervention Services team, GHHI will arrange for a contractor to complete the Scope of Work. All costs for modifications whether by the GHHI home modification team or by outside contractors will be paid for by the project with the grant funding. As is standard procedure for GHHI, there will be a post-intervention quality control assessment conducted by an Assessor immediately after the injury prevention intervention to verify that all measures on the Scope of Work were installed properly and meet HUD and project standards. Any discrepancies will be resolved. GHHI will document all costs, both labor and supplies, associated with completing the Scope of Work.

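### The HV2–HV3 maintenance comparison has no in-place baseline for modifications installed by GHHI or its project-paid contractors, because that work is done after HV2

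*Protocol article*

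**What the plan says.** The Data analysis plan singles out maintenance as a main interest and states how it will be studied: "which will be examined by comparing HV2 and HV3 data; this will be an analysis of proportion of modifications still in place at HV3". It then plans regressions of the hazard and maintenance outcomes on several variables, one of which is installer, with homeowner/tenant and GHHI as its categories.

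The Procedures section gives the order of events:

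- "Home Visit 2 (HV2) will occur approximately 30 days after HV1".
- At HV2 the Assessor reinspects, "completing another CHASE Home Assessment Form to identify which hazardous item(s) the participants were able to modify on their own".
- If hazards remain, "the Assessor will draft a Scope of Work for completion of the needed modifications and arrange a time to return to the home"; on that later visit GHHI's own team does the work. Work beyond that team's capacity goes to a contractor arranged by GHHI and paid by the project.
- After that work, "there will be a post-intervention quality control assessment conducted by an Assessor immediately after the injury prevention intervention", which checks the items on the Scope of Work.
- HV3 follows three months after the last modification is finished.

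Study design and setting describes the first two visits differently. It says they serve, among other things, to identify hazards "and assess the short-term maintenance of home modifications".

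**The concern.** A maintenance analysis needs a record that the modification was in place at the start and a second record of whether it is still there. For resident work, HV2 supplies the first record. For work by GHHI or a project-paid contractor it cannot, because that work has not yet been done. At HV2 those items carry a fail.

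This matters because the third study objective, at the end of the Background, asks about consistency of maintenance by residents and by staff. The regression on installer is where that question would be answered. If the named comparison is programmed as written, the staff half of the objective has no valid baseline, and an overall maintenance rate would describe resident work only.

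**Working it through.** **Inputs from the protocol article.** The order of events is HV1, resident work, HV2 (about 30 days), Scope of Work, GHHI or contractor work, quality control, and HV3 (three months after completion). The comparison named for maintenance is HV2 with HV3. The regression variable is installer, with GHHI as a category.

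**Step 1: the article's own figure.** The only calculation given is the detectable change of 1.36 hazards (Sample size section). With N = 300, SD 8.4 taken as the SD of paired differences, two-sided α = 0.05 and 80% power:

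(1.960 + 0.842) × 8.4 / √300 = 1.36.

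It reproduces. It concerns HV1 versus HV3, so the present point does not touch it.

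**Step 2: item histories.** Take an item that failed at HV1.

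| Who fixed it | HV2 | Quality control | HV3 if kept | HV3 if lost | HV2–HV3 pattern |
|---|---|---|---|---|---|
| Resident, before HV2 | pass | not applicable | pass | fail | pass–pass or pass–fail |
| GHHI or project-paid contractor, after HV2 | fail | pass | pass | fail | fail–pass or fail–fail |

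The first row is a maintenance history. In the second row, from HV2 and HV3 alone, a kept fix looks like a new installation and a lost fix looks like one never made. If the denominator is items passing at HV2, the second row disappears and the GHHI category of the installer variable is empty.

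**Step 3: how far a resident-only figure could be off.** The article gives no retention rates and no split of the work, so everything here is assumed: 10 hazards per home at HV1, all eventually fixed; resident share s = 25%, 50% or 75%; resident retention 80%; GHHI retention 60% or 90%. True overall retention = s × 0.80 + (1 − s) × GHHI retention. A denominator of items passing at HV2 reports 80% throughout.

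| Resident share | GHHI items omitted (of 10) | True rate, GHHI 60% | True rate, GHHI 90% |
|---|---|---|---|
| 25% | 7.5 | 0.20 + 0.45 = 65% | 0.20 + 0.675 = 87.5% |
| 50% | 5.0 | 0.40 + 0.30 = 70% | 0.40 + 0.45 = 85% |
| 75% | 2.5 | 0.60 + 0.15 = 75% | 0.60 + 0.225 = 82.5% |

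The reported 80% is between 15 points too high (80 − 65) and 7.5 points too low (87.5 − 80). If both groups retain equally, the overall rate is not biased, but the installer contrast still has no GHHI observations under that denominator.

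**Step 4: time at risk.** HV3 is timed from completion of all work. Let d be the delay from HV2 to completion of the GHHI work in a home. GHHI items are followed for about three months from quality control. Resident items in the same home are followed for three months plus d from HV2. The article does not give d. Any positive d gives resident items longer to fail, so a correct baseline alone does not make the two installer groups comparable.

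**The case against.** The strongest reply is that the data described do allow the analysis. Every item on the Scope of Work is to be checked at quality control and any discrepancy resolved, and HV3 waits until all work is complete. An item that failed at HV2 and was on the Scope of Work was therefore in place before HV3 by design, so a pass at HV3 means kept and a fail means lost. HV2 is then what separates resident items from GHHI items. The maintenance outcome is also worded as "this will be an analysis of proportion of modifications still in place at HV3 by outcome variable and by modification options", and the installer regression shows that GHHI work is meant to be counted. Nowhere does the article restrict the denominator to items passing at HV2.

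Much of this stands, and it rules out several stronger readings that a reader might infer:

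- *The installer comparison cannot be estimated.* Not supported. It can be recovered from the Scope of Work and quality control records.
- *The quality control data go unused.* Not shown. The maintenance analysis does not name them, which is not the same as excluding them.
- *All professional work comes after HV2.* Too broad. Under Procedures, a caregiver may engage a contractor after HV1. The statement holds for GHHI and project-paid contractor work.
- *A falling hazard count from HV2 to HV3 would hide losses.* Changes in mean hazard count are planned only for HV1–HV3 and HV1–HV2.

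What does not stand is treating this as detail left to a fuller document. The article names a specific pair of visits, and for one of the two installer groups the first of that pair precedes the installation. The route that rescues the analysis needs records which the named comparison does not include. The wording and the evident intention conflict.

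**Conclusion.** The point holds as a conflict between the stated comparison and the sequence of visits. HV2 versus HV3 is a valid maintenance comparison for items fixed by residents, including through a contractor they hired. It has no in-place baseline for items fixed by GHHI or a project-paid contractor. Taken literally, it drops or misreads those items and is incompatible with GHHI as an installer category.

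The size and direction of any bias cannot be determined from the article. The 65% to 87.5% range against a reported 80% rests wholly on assumed shares and retention rates, and on reading the denominator as items passing at HV2. It shows that the error could go either way, not what it will be.

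The consequence is confined to the maintenance analysis and its regression. The HV1–HV3 test, its sample size and the HV1–HV2 analysis of what caregivers can do themselves are unaffected. The correction is still worth making before analysis, because it is needed for the objective on maintenance by residents and staff.

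**What to change.** In the Data analysis plan, replace the HV2-with-HV3 comparison by a comparison of the verified-completion record with HV3:

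1. **Denominator:** each CHASE item that failed at HV1 and was later verified as fixed. Verification is at HV2 for items completed by residents (including by a contractor they hired), and at the post-intervention quality control assessment of the Scope of Work for GHHI or project-paid contractor items.
2. **Outcome:** pass or fail of that item at HV3, reported by installer.
3. **Installer comparison:** account for time from verification to HV3, which is longer for resident items in homes that then wait for GHHI work.
4. **Study design and setting:** describe HV2 as assessing resident completion rather than maintenance.

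The cost is a change of wording and entry of the quality control results item by item. The assessment itself is already standard GHHI procedure. No visit, instrument or sample size changes.

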#### CHASE Home Assessment Form and Family Feedback Form

The CHASE tool is a 35-item home injury hazard assessment organized into 15 subdomains (e.g., carbon monoxide risks, falling furniture, and hot water burns). Each item on the CHASE tool assesses whether a household passes or fails to address a household hazard, offers facts about the hazard, and gives user-friendly, nationally accepted best practices and information on how to remediate the hazards to make homes safer. For example, the medicine storage subdomain includes the item, “All prescription and over-the-counter medicines have childproof caps,” with the response options, “Yes” or “No.” For this project, the CHASE tool was adapted into the CHASE Home Assessment Form, which includes all elements of the CHASE tool but further allows the housing assessor to specify home modifications needed to remediate the hazards during home inspections.

The Family Feedback Form is a companion form that uses information transferred from the CHASE Assessment Form to provide participants a short description of each home injury risk being assessed and why it is important, whether the home passed or failed each item and why, and next steps to be taken. In some instances, the form recommends calling a contractor for changes that the parent or caregiver cannot complete on their own. The Family Feedback Form will guide the educational intervention that will be delivered with the goal of preparing the parent or caregiver to initiate recommended changes. For example, on the topic of poison storage, the housing assessor will give the participant a lock box or cabinet locks and show them how to install it. Accordant with the HBM, these instructions are intended to increase the self-efficacy of the participant by showing them how to install and/or use a home safety product. The “Why This is Important” column of the Family Feedback Form also contains a perceived risk and/or an efficacy message that will be reiterated to the participant to reinforce the messages by a credible individual.

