### Sample size

A total of 300 homes (total of 900 home visits) will be studied in Baltimore City and Baltimore County, which will be referred from GHHI’s existing housing programs: Using a paired analysis of the number of hazards at Time 1 (HV1) versus Time 2 (HV3) with *N* = 300, *α* = 0.05, and assuming standard deviation 8.4 (Posner et al. 2004), we will have 80% power to detect a change in the mean number of hazards of 1.36.

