This study is subject to limitations. First, our procedures which provide 30 days for the families to complete repairs on their own followed by a reinspection and then modifications provided by GHHI limit our ability to know what modifications families would make on their own without knowing that GHHI would return to make the modifications. We designed it this way with the hopes of learning what families could modify easily on their own to inform expectations and cost estimates for future work. We recognize that our estimates will be conservative. It is additionally important to acknowledge that this study does not utilize an experimental design. Although the standardization of the CHASE assessment promotes strong internal validity, the limited data produced from a pediatric population in one geographic area limit the generalizability of the data. Future work should utilize the tool in other programs that have access to the homes of young children, such as pediatric home visiting programs including those funded by Title V Maternal and Child Health Block Grants, which serve 140,000 households per year (Health Resources Services Administration 2022). In addition, future work should consider targeting housing risks beyond the pediatric population. Previous work from the Community Aging in Place—Advancing Better Living for Elders (CAPABLE) program, demonstrated a reduction in older adult falls through the delivery of a comprehensive program which included a handyman to address fall risks in the home (Szanton et al. 2014). Translating the comprehensive injury measures included on the CHASE tool to older adults could assist with aiding older adults to age in place. Further, it is unclear how overall housing quality will mediate the benefit of the CHASE measures. Therefore, after the completion of this implementation study there will still be the need to conduct either an experimental (e.g., randomized trial) or quasi-experimental (e.g., matched case–control) outcome study to determine the efficacy and cost effectiveness in reducing unintentional injuries in the home. Upon completing this implementation study, we will better understand the necessary steps for large scale adoption and implementation of the CHASE assessment and modification protocols in existing housing inspection programs and home visiting programs.

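### The hazard-outcome regressions list no HV1 hazard count, so their associations mix how many hazards a home started with and how well those hazards were remedied

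*Protocol article*

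**What the plan says.** The Data analysis plan describes several hazard outcomes: the number of hazards per home at each visit, a pass score over all items, the prevalence of each hazard, and the HV1-HV3 change ("A paired analysis will be used to test the change in mean number of hazards present between HV1 and HV3"). It separately describes maintenance as the proportion of modifications still in place at HV3.

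It then announces "regression analyses to explain the hazard and maintenance outcomes described above as a function of referral source, sociodemographic characteristics, housing, knowledge, installer", a list that closes with satisfaction. Neither this list nor the list of additional variables just before it contains the HV1 hazard count. The plan does not say which hazard outcome is regressed.

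Three other places bear on the point:
- On the instrument: "The CHASE tool is a 35-item home injury hazard assessment organized into 15 subdomains". Each item is pass or fail.
- Under Procedures, hazards left at HV2 go to installation paid for by the project, followed by a check "to verify that all measures on the Scope of Work were installed properly and meet HUD and project standards".
- The Discussion expects older homes to carry greater risks, so one listed variable, housing, is expected to be related to the starting count.

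**The concern.** The Abstract gives the regressions two purposes: to examine maintenance, and to find what is associated with good outcomes. For the second, a reader will take a coefficient on the hazard outcome as showing in which homes the programme works better or worse.

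Without the HV1 count, that reading is unsafe. The number of a home's starting hazards that can be removed is capped by what it failed at HV1. A variable that goes with more hazards at the start will therefore go with a larger reduction and, unless remediation is almost complete, with more hazards remaining. The first looks like greater benefit and the second like less, from the same homes and the same chance of repair.

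The installer variable is exposed as well. The professional team is called in when a family has not cleared everything by HV2, which is likelier when there was more to clear.

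**Working it through.** **The plan's own figure.** The Sample size section has "A total of 300 homes (total of 900 home visits) will be studied", "assuming standard deviation 8.4" and "we will have 80% power to detect a change in the mean number of hazards of 1.36". The paired formula is (z for two-sided 0.05 + z for 80% power) × SD / √N = (1.960 + 0.842) × 8.4 / √300 = 1.359. The stated 1.36 reproduces. It concerns the paired test, where each home is its own control, and this point does not touch it.

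**Inputs.** From the protocol: 300 homes and 35 items. Assumed, because the protocol gives no CHASE counts: the HV1 difference D between two kinds of home, the share p of HV1 hazards fixed by HV3 (equal in both kinds), and the share r of HV1-passed items that newly fail.

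**By hand.** A home with H hazards at HV1 has expected HV3 count (1 − p)H + r(35 − H). Between the two kinds of home:
- difference in HV3 count = (1 − p − r) × D
- difference in reduction (HV1 minus HV3) = (p + r) × D

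The two sum to D. The same identity holds for least-squares coefficients with any common covariates: the coefficient on reduction plus the coefficient on HV3 count equals the coefficient on HV1 count. With D = 2 and r = 0.02:

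| p | More hazards left at HV3 | More hazards removed |
|---|---|---|
| 0.60 | 0.38 × 2 = 0.76 | 0.62 × 2 = 1.24 |
| 0.80 | 0.18 × 2 = 0.36 | 0.82 × 2 = 1.64 |
| 0.95 | 0.03 × 2 = 0.06 | 0.97 × 2 = 1.94 |

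**Chance of a significant coefficient.** Take the planning SD of 8.4 as the SD of change and two groups of 150. The standard error is 8.4 × √(2/150) = 0.97. A difference of 1.64 gives 1.64 / 0.97 = 1.69, and Φ(1.69 − 1.96) is about 0.39. So about 39% of studies would report the factor as significant, although the chance of repair is the same in both groups.

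**Simulation with other assumed inputs.** 300 homes and 1,000 runs per setting; mean HV1 count about 12 of 35, with at least 1 per home; a binary factor in half the homes adds about 3 hazards at HV1 and does not affect repair; repair probability varies between homes around p; no new failures; least squares with robust errors. Change is HV3 minus HV1, so negative means a larger reduction. Percentages are runs significant at 0.05.

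| p | HV3 count, unadjusted | Change, unadjusted | Either outcome, HV1 count added | Proportion of HV1 hazards remedied |
|---|---|---|---|---|
| 0.3 | +2.09 (99.8%) | −0.91 (78.5%) | −0.007 (5.1%) | 0.000 (5.0%) |
| 0.5 | +1.50 (96.0%) | −1.52 (95.6%) | −0.004 (4.2%) | 0.001 (4.3%) |
| 0.7 | +0.90 (78.0%) | −2.07 (99.0%) | −0.004 (6.4%) | 0.000 (5.8%) |
| 0.9 | +0.30 (32.7%) | −2.69 (99.7%) | 0.000 (5.0%) | 0.000 (5.6%) |

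With the HV1 count in the model, HV3 count and change give the same coefficient for the factor, so the open choice between them stops mattering.

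**The case against.** Several objections have force.

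- **Scope.** The regression sentence also covers maintenance, which the plan singles out as of particular interest. That outcome is already a proportion and does not depend mechanically on the HV1 count. A reader might infer that all the regressions are affected; they are not.
- **Real differences.** In these examples, homes with more hazards at the start really do lose more and really do have more left. As descriptions of absolute counts the coefficients are correct. They mislead only when read as success in remedying hazards. A reader might infer that the regressions measure starting load instead of remediation; in fact they mix the two, in shares set by p.
- **Silence.** The plan does not name the regressed hazard outcome, so the use of a raw count or change is inferred from its reference back to the outcomes already described. It also promises further analyses of individual hazards and modifications. A fuller plan might add the HV1 count. Still, the article prints a specific list of explanatory variables, and every hazard outcome before it is a count, a score on the full item total, a prevalence or a change.
- **Near-complete repair.** If almost everything is fixed, the HV3 difference vanishes (0.06 at p = 0.95), and a proportion remedied also has little left to explain. The change score is then at its most distorted (1.94 of the 2-hazard difference).
- **The check favours the remedy.** The simulated data have a repair chance unrelated to the starting count and no scoring error. In the study, an Assessor scores HV1 and a Research Assistant scores HV3, so an item wrongly failed at HV1 could count as remedied.
- **Housing quality.** The Discussion says "it is unclear how overall housing quality will mediate the benefit of the CHASE measures", and a reader might infer that these regressions are meant to settle that. The text defers the question to a later experimental or quasi-experimental study.

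**Conclusion.** The point holds for the hazard-outcome regressions only. As listed, their explanatory variables omit the HV1 hazard count, so associations with the HV3 count or the HV1-HV3 change combine starting load and remediation and can carry opposite messages. The direction follows from algebra. The size does not come from the protocol: with a 2-hazard HV1 difference, 2% new failures and 60% to 95% fixed, it is 1.24 to 1.94 hazards on the change and 0.76 to 0.06 on the HV3 count. It would be smaller for a variable less closely linked to the starting count and nil for one unrelated to it. The paired HV1-HV3 test, the sample size and the maintenance proportion stand as they are.

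**What to change.** In the Data analysis plan, name the hazard outcome to be regressed and do one of the following:

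1. If the HV3 count or the HV1-HV3 change is used, include the HV1 hazard count as a covariate. A log offset is unsuitable because it fails for homes with zero hazards at HV1.
2. Model the number of HV1-failed items that pass at HV3 out of those failed at HV1, with a variance robust to overdispersion and the same explanatory variables. Report newly failed items separately.

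Add a sentence that unadjusted differences in counts may be shown as description but are not read as predictors of remediation success.

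This is a free improvement: a change of wording only, since the CHASE form is already completed at HV1 and HV3. The second option has a small downside. Homes with no failed item at HV1 drop out, the result is no longer a count difference, and there is little to explain if nearly all hazards are fixed.
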